## Abstract

**Background:**

In the face of extensive waiting times for outpatient psychotherapy, prescriptible digital health applications (DiGA) are a useful and effective addition to the range of available therapy options for patients with mild to moderate depression. However, older adults face a particular challenge in implementing DiGA since higher age is a decisive predictor of lower digital health literacy. The necessity of an independent use of the prescribed DiGA is therefore associated with challenges for older patients and providers. In practice, it is crucial not to leave patients, especially older adults, alone after prescribing, but to maintain close contact to overcome technical and motivational barriers and to ensure that the novel application is used. However, this is difficult for physicians and psychotherapists due to the critical healthcare system situation in Germany described above. Another support system is needed. Hence, the main hypothesis of this study is that the additional implementation of digital nurses leads to a higher percentage of older patients with depressive symptoms starting DiGA use compared to a prescription and information alone.

**Methods:**

Two DiGA for mild to moderate depression in older patients were available and permanently approved at the time of the funding application. Using the most suitable one of them, as shown in a pilot study, the feasibility of implementation will be examined within a randomized proof of concept study. In our study, a digital nurse is trained to support patients with depression in using a DiGA. The main outcome is DiGA use (first session started: yes/no) after 8 weeks. Major secondary outcomes are patient-relevant outcomes, feasibility of recruitment and intervention, and factors moderating the effect or predicting DiGA use in the target group. Best practice guidelines will be elaborated on how to support and improve DiGA prescription and successful use in this population.

**Discussion:**

In Germany, the approved DiGA are currently little used, especially by people with a low digital affinity. This proof of concept study will use the example of older people with depressive disorders to show whether it is possible to increase the usage rate of a DiGA with the support of a digital nurse so that a DiGA can become a serious therapy option.

**Trial registration:**

DRKS: DRKS00033535. Registered on February 2, 2024.

## Administrative information

Note: the numbers in curly brackets in this protocol refer to SPIRIT checklist item numbers. The order of the items has been modified to group similar items (see http://www.equator-network.org/reporting-guidelines/spirit-2013-statement-defining-standard-protocol-items-for-clinical-trials/).

## Introduction

### Background and rationale {6a}

In the face of extensive waiting times for outpatient psychotherapy, digital health applications are a useful and effective addition to the range of available therapy options for patients with depression and other psychiatric disorders, which should be considered in treatment planning [1, 2]. Smartphone apps have been shown to reduce depressive symptoms in patients [3] and can therefore be used to support treatment or bridge waiting times [4]. Nuij et al. [5] examined smartphone apps in inpatient depression treatment and found that apps in addition to behavioral therapy-based psychotherapy improved the severity of depressive symptoms. This effect is also seen after discharge from inpatient treatment, underscoring the usefulness of digital applications in outpatient care as well.

In addition to general health apps, so-called DiGA (digital health applications) exist in Germany, which can be prescribed by physicians and psychotherapists. The prescription of a DiGA is possible at the expense of the statutory health insurance and in some cases also the private health insurance since the Digital Health Care Act (Digitale-Versorgung-Gesetz, DVG) came into force on 19th December 2019 [6]. According to a report of the Central Association of the Statutory Health Insurance (GKV-Spitzenverband), around 203,000 DiGA were prescribed and approved by the statutory health insurance funds in the period from the 1st of September 2020 to the 30th September 2022 (Central Association of the Statutory Health Insurance [7]).

DiGA are low-risk medical devices (class I or IIa). They have been tested for their safety, data protection, medical quality, performance, interoperability requirements, and positive care effects through scientific studies as part of a procedure conducted by the Federal Institute for Drugs and Medical Devices (BfArM) [8]. This is done in a so-called fast-track procedure, in which a decision is to be made after only 3 months. If the vote is positive, the DiGA are included permanently or temporarily (for 1 year) in the DiGA directory of the BfArM. In June 2024, 64 DiGA were listed in the DiGA database (https://diga.bfarm.de/de/verzeichnisExternalRef>), of which 35 are permanently included. Most DiGA are from the “mental illness” category (currently 27), thereof 7 target depressive disorders. At the time of study planning, the BfArM DiGA list included two permanently approved DiGA for the treatment of people with depressive disorders. One was approved for use in mild as well as moderate depressive disorders, the other had an approval for mild, moderate, and severe depressive disorders. Both DiGA are based on cognitive behavioral therapy (CBT) approaches, psychoeducation, self-monitoring, and emotion regulation exercises, which individuals go through independently via a web application or app. The programs are designed to be interactive and adapt to the user's responses and interactions (e.g., interactive dialog). Motivational emails are sent for support or basal email contacts with psychological counselors from the manufacturers are offered. Recommended durations of use are comparable and are approximately 90 days and 12 weeks, respectively. Weekly usage durations of 1–2 h are recommended. Our working group is currently testing in a pilot study which of the two DiGA is more suitable for people aged 60 and older in a qualitative pre-study (DRKS registration no. DRKS00033640, [9]). This DiGA will then be used in this RCT.

A survey of general practitioners published in 2020 revealed that many physicians had little experience using health apps in general at that time, and 63% of respondents also had a low or very low willingness to prescribe DiGA. It should be noted that 51% of respondents indicated that their knowledge of the DVG was somewhat poor, 12% rated it as poor, and 12% were unaware of the DVG. A study on experiences and observations of physicians regarding the use of DiGA in 2022 showed that the prescribed applications were rated as useful [10]. Positive care effects were observed, these concern the improvement of compliance, mobility, and education as well as weight reduction (using respective DiGA). Suggestions of interviewees include further optimization of usability, systematic further training of physicians on DiGA, and the expansion of gamification elements. Physicians have so far lacked well-founded information about DiGA.This indicates that providers likewise need to be empowered to prescribe health apps and DiGA and assess the benefits [11].

International results underline the findings that the use of health apps is significantly less likely among older than younger people [12]. Health apps tend to be used by younger, educated individuals with digital health literacy, while older age and low digital health literacy are associated with non-use of health apps [13]. The authors concluded that the benefits of expanding digital health offerings do not reach vulnerable groups such as the older population that would need to be focused on. Based on current data on the use of DiGA in Germany, it is known that the frequency of DiGA use is significantly lower after the age of 60 [14]. The barriers for older adults with depression to use DiGA should thus be taken into account. Higher age was found to be a decisive predictor of low digital health literacy in a comprehensive study of digital health literacy among the population in Germany [15]. Digital health literacy is the ability to find, understand, assess, evaluate, and apply health-related information in relation to digital health and information services [16]. It combines traditional, health, information, science, media, and computer literacy [17] and can therefore be understood as a combination of health and media competencies. Older persons thus might have a high need for assistance and guidance in (starting) DiGA use. In this context, a secondary analysis of the EVIDENT study, exploring the efficacy of a DiGA in addition to treatment as usual, revealed interesting results. Older age and higher depressive symptoms were associated with higher usage time. Higher adherence predicted a greater reduction in depressive symptoms over 12 weeks. However, these results could mostly be explained by receiving support [18]. In the context of older patients, studies of applicants showed that in the course of installing and administering digital consumer health-related products, friends or family members were consulted in a large number of cases [19]. Prescribing and empowering independent use are therefore associated with challenges for patients and providers [20]. In practice, it is crucial not to leave patients alone after the prescription, but to ensure in close contact that the novel application is used and that this is done in the intended manner [21].

It is noteworthy, the above-mentioned EVIDENT study examined persons up to 65 years of age. Results thus refer to younger age ranges among older adults. Likewise, the focus in the investigation of apps on depression is mainly on younger individuals [22, 23]. The participants in the studies examining the efficacy of the two approved DiGA [24, 25] were up to 65 years of age. Adults aged 65 years and older might need even more support to be able to use a DiGA.

With the intervention of a digital nurse, we want to create a standardized offering in our study for all those adults aged 60 years or older, similar to the above-mentioned frequently used support from relatives. The digital nurse is a person who has been trained to support older people in the commissioning and use of DiGA. Studies investigating the efficacy of support in the use of health apps usually focus on therapeutic support and aspects of motivation for regular use rather than on technical support to enable access to and usability of the prescribed DiGA in the first place. Evidence on the value of digital nurse support aiming at improving the usability of DiGA in older adults is lacking.

### Objectives {7}

Against this background, the primary objective is to evaluate whether it is possible to increase the usage rate of a DiGA with the support of a digital nurse in a population of patients aged 60 or above with depressive symptoms. Further objectives are to improve patient-relevant outcomes, to explore the feasibility of recruitment and intervention in different settings, and finally to explore factors moderating the effect or predicting DiGA use in the target group.

### Trial design {8}

The main hypothesis of the trial is: The support of digital nurses in the process of prescribing a DiGA leads to a higher percentage of DiGA use in older patients with depressive disorders compared to treatment as usual. This hypothesis will be tested in a multi-center randomized superiority trial (RCT) with two equally sized arms and randomization on patient level. This RCT is used for investigation of the feasibility of recruitment and implementation, and proof of concept.

The intervention consists of the additional offer of a digital nurse (intervention group) compared to treatment as usual (control group) in patients who are prescribed a DiGA. The success of the intervention will be measured 8 weeks after randomization. A pilot study preceding this RCT aimed to identify the most appropriate DiGA for the target population that would subsequently be used in the RCT. The pilot study is described in a separate study protocol [9]. DiGA are generally subject to full reimbursement by the German statutory health insurance after prescription. Participation in the trial is cost-free. Access to the DiGA is generally valid for 3 months after the start of DiGA processing. If interested, a re-prescription can also be made by the supervising physician after the end of the study. The support provided by the digital nurse ends at the end of the study period.

## Patient involvement

Patients were involved in the design of the RCT with regard to the choice of the DiGA. Patients tested and evaluated the DiGA available for the target group and thus made a significant contribution to the potential success of the interventions. There was no further public involvement.

## Methods: participants, interventions, and outcomes

### Study setting {9}

Recruitment will take place across sectors (outpatient and inpatient) in three academic hospitals (geriatrics, psychiatry, and psychosomatics) and selected, collaborating general practitioner practices in North Rhine-Westphalia, Germany.

### Eligibility criteria {10}

#### Inclusion criteria

The aim is to recruit a heterogeneous patient population to investigate possible influencing factors and moderators on DiGA use. During the recruitment process, detailed documentation of the screened patients will take place to investigate factors for non-participation.

To be eligible to participate in this study, an individual must meet all the following criteria:Provision of signed and dated informed consent formAge ≥ 60 yearsMild to moderate depressive disorder based on ICD-10 codes F32.0, F32.1, F33.0, F33.1Access to digital device (desktop computer, tablet, or smartphone) that enables DiGA useStated willingness to comply with all study procedures and availability for the duration of the study

#### Exclusion criteria

An individual who meets any of the following criteria will be excluded from participation in this study:Incapacity to consentCurrent suicidalitySevere auditory and/or visual impairmentInsufficient German language skillsPresence of moderate to severe dementiaPresence of a bipolar disorder, schizophrenia, or other severe psychiatric illnesses that make participation impossibleAdvanced somatic terminal illnessCurrent participation in another intervention studyCurrent or former use of any DiGA for depression

### Who will take informed consent? {26a}

After pre-screening of eligibility (see item 15, recruitment), final eligibility of patients ≥ 60 years with a mild or moderate depression is assessed during the baseline study visit. If a patient is eligible, a clinician informs the patient in detail about the study and study participation. The patient will be given time to read the patient information and consent material and to ask questions. If the patient is willing to participate, written informed consent is provided.

### Additional consent provisions for collection and use of participant data and biological specimens {26b}

No additional consent provisions for the collection and use of participant data and biological specimens are necessary.

## Interventions

### Explanation for the choice of comparators {6b}

The control intervention is treatment as usual. After DiGA prescription, patients receive a short information by their treating physician, and the manufacturer’s information film about the DiGA is shown. The further process of activating the DiGA and its use are the responsibility of the patient.

### Intervention description {11a}

In addition to a short information by the treating physician after DiGA prescription and the manufacturer’s film, the intervention group receives the offer of regular individual support by a digital nurse who accompanies and supervises the process of request to the health insurance companies, the installation of the app/navigation to the website until the first use of the DiGA up to 8 weeks according to the needs of the patients. The consultations are offered in different ways depending on the patient's needs: by telephone, via video call or face to face. Support is actively offered to patients at least once a week. The digital nurses are trained particularly in the process of prescription and establishing contact with the DiGA manufacturer and the health insurance company. Furthermore, the digital nurses are trained in the installation and application of the DiGA. Within the counseling process, the digital nurses should respond attentively and sensitively to the needs of the participants. They will therefore be trained in motivational interviewing techniques like active listening and change talk. The digital nurses also monitor the emotional state of the participants in order to identify mental crises and suicidal tendencies, that might necessitate intensive care in inpatient settings as well as exclusion from the study.

A guideline is developed that defines the counseling process and the care options. Checklists will be used to ensure fidelity to the guideline. In order to develop best practice guidelines number of sessions, mode and duration of intervention, total support time, and discussed topics will be documented during each counseling session.

The trained digital nurse supports the individual participant in using the DiGA for up to 8 weeks or until the first use of the DiGA, whichever comes first (intervention phase). This means that at the time the participant is able to start the first session of the DiGA, the support of the digital nurse ends. However, the digital nurse will be available to patients until week 16 if they have any problems or questions regarding the DiGA application (follow-up phase).

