### Criteria for discontinuing or modifying allocated interventions {11b}

Participants are able to discontinue the study intervention at any time without giving reasons and without suffering any disadvantage, as stated to them prior to informed consent. The study intervention will be discontinued, if it becomes apparent that the system requirements for using the DiGA are not met. Furthermore, study intervention (seeking contact through the digital nurse) will be stopped, if it becomes apparent that the patient's mental or somatic health has deteriorated significantly, and the patient is currently unable to use the DiGA.

When a subject discontinues from the study intervention but not from the study, the remaining study assessments will be completed as indicated by the study protocol.

The data to be collected at the time of study intervention discontinuation will include the following:Point in timeThe reason(s) for discontinuing the intervention.If possible, the primary endpoint and depressive symptoms at the time of discontinuation.

Thereafter, the participant will be included in all future scheduled assessments, even though not participating in the intervention.

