### Strategies to improve adherence to interventions {11c}

During the intervention phase, there are no restrictions on the number, duration, or type of contacts (telephone, videocall, face to face). The meetings are deliberately organized according to the patients’ needs in order to improve adherence. However, the digital nurse will contact the patient at least once a week at the beginning of the intervention period.

The mode of administration, number, and total support time for each participant will be documented and evaluated.

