#### Primary and secondary endpoints

For the primary endpoint, the main aim is to estimate the odds ratio (OR) of DiGA use with digital nurse support vs. unsupported prescriptions. The confirmatory analysis will be conducted in the full analysis set (FAS, see below) based on the intention-to-treat (ITT) principle. The analysis of the primary endpoint is carried out using a logistic regression model. In addition to the intervention group, the model also includes age, gender, and the recruiting center as well as possible other factors as covariates. One-sided *p*-value corresponding to the hypothesis given above, estimated OR and corresponding one-sided confidence interval will be reported. One-sided *p*-value will be calculated as half of the *p*-value from the fitted model output.

Analyses of all secondary outcomes are exploratory and will be done as complete case analyses, meaning that only cases with available data for the analysis are included. Analysis of the secondary efficacy outcomes will be undertaken following the same framework as the primary outcome model, particularly using the same covariates in the models. For each continuous outcome including the PHQ-9 and SUS, a linear regression model will be fitted. For the analysis of PHQ-9, the baseline value is included in the model as an additional covariate. The estimates for the group effect with accompanying 95% confidence intervals and two-sided *p*-values will be reported. Details of the models will be specified in the statistical analysis plan (SAP).

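### A crisis detected by the digital nurse may end either in exclusion from the study or in continued follow-up, and only the intervention arm has the nurse

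*Protocol article*

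**What the plan says.** Intervention description {11a} gives the nurses a monitoring task: to "identify mental crises and suicidal tendencies, that might necessitate intensive care in inpatient settings as well as exclusion from the study". The wording is permissive; exclusion may follow but is not required. The same section ties the active support to the period before first use: "at the time the participant is able to start the first session of the DiGA, the support of the digital nurse ends". After that the nurse remains reachable until week 16 if the patient has problems or questions.

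Section {11b} sets the discontinuation rules. Nurse contact stops if the patient's mental or somatic health "has deteriorated significantly, and the patient is currently unable to use the DiGA". The time point and reason are then recorded and, "If possible, the primary endpoint and depressive symptoms at the time of discontinuation". The section goes on: "Thereafter, the participant will be included in all future scheduled assessments, even though not participating in the intervention". This protection is written for patients who leave the intervention while staying in the study. No criterion for leaving the study itself on clinical grounds is listed.

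On contact by arm, {11c} says that "the digital nurse will contact the patient at least once a week at the beginning of the intervention period". For controls, {6b} describes physician information and a film, and then: "The further process of activating the DiGA and its use are the responsibility of the patient".

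On analysis, the section on primary and secondary endpoints states: "Analyses of all secondary outcomes are exploratory and will be done as complete case analyses". Missing values of the primary endpoint are to be imputed, with the method left to the SAP.

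**The concern.** A mental crisis that needs inpatient care will often also be a significant deterioration that leaves the patient unable to use the DiGA for the time being. A site could then follow {11a} and exclude the patient, or follow {11b} and keep collecting outcomes. Nothing in the article says which applies.

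The choice matters because the detection route is not balanced. Only intervention patients have a nurse looking for crises, and regular contact runs mainly until first use. Patients found this way would therefore mostly be people who have not started, which is the unfavourable value of the primary endpoint, and they would probably have high PHQ-9 scores. If they leave the study, the remaining intervention arm looks somewhat better on both counts.

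Week-16 DiGA use and PHQ-9 are analysed on complete cases, so excluded patients simply drop out of them. Both are exploratory, but the observed PHQ-9 difference is one of three inputs that {20b} names for judging the feasibility of a multi-center trial, beside recruitment rates and patient satisfaction. For the week-8 primary endpoint, a non-start that could have been recorded may become a value to be imputed.

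**Working it through.** **The plan's own figure.** Sample size {14} assumes 30% vs 50%, Fisher's exact test, one-sided 5%, power 80%. Exact power is 79.8% at 83 per group and 80.5% at 84, so the stated 84 reproduces. With 15% dropout, 84 / 0.85 = 98.8, so 99, which the plan rounds to 100. This point disputes none of these figures.

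**The two rules side by side.**

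| | {11a} | {11b} |
|---|---|---|
| Trigger | crisis or suicidal tendency seen by the nurse | significant deterioration and currently unable to use the DiGA |
| Consequence | inpatient care and exclusion from the study, both possible | nurse contact stops |
| Outcome collection | not stated | continues as scheduled |
| Arm | intervention only | in effect intervention only, since what stops is nurse contact |

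The triggers are not identical, but they overlap.

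**Size for a yes/no outcome.** From the plan: 100 per arm and a 30% start rate, here set equal in both arms (the null). Assumed, because no crisis rate is given: a share f = 1% or 2% of intervention patients is excluded, of whom a share s would have started. The remaining arm's rate stands in for theirs. That is what a complete-case analysis of week-16 use does (30% at week 16 is a further assumption), and what imputation at the arm's observed rate would do at week 8.

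- Observed rate: p_I = (0.30 − f·s) / (1 − f), with n_I = 100(1 − f).
- One-sided type I error ≈ 1 − Φ(1.645 − log OR / SE), where SE² = 1/[n_I·p_I(1 − p_I)] + 1/[n_K·p_K(1 − p_K)].

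For f = 0.02 and s = 0: p_I = 0.30/0.98 = 0.306, OR = 1.029, log OR = 0.0290, SE = 0.309, ratio 0.094, type I error = 1 − Φ(1.551) = 6.0%.

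| Scenario | f = 1% | f = 2% |
|---|---|---|
| All non-starters, no control loss | 5.5% (OR 1.01) | 6.0% (OR 1.03) |
| One in ten would have started, no control loss | 5.3% | 5.7% |
| All non-starters, control loses half as many | 5.2% | 5.5% |
| Equal losses in both arms | 5.0% | 5.0% |

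A simulation of 400,000 runs gave 5.5% and 6.0% for the first row, and 5.0% for both when excluded patients were counted as non-starters.

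As an outer bound, 5 exclusions per 100, all non-starters and with no control loss, give OR 1.08 and a type I error of 8.0% by a z-test or 5.8% by Fisher's test. With no exclusions those tests run at 5.1% and 3.7%.

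**Size for PHQ-9.** Assume that excluded patients score d = 5 to 8 points above the arm mean. The complete-case intervention mean then falls by f·d/(1 − f):

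- smallest: 0.01 × 5 / 0.99 = 0.05 points;
- largest: 0.02 × 8 / 0.98 = 0.16 points.

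With an assumed SD of 5, baseline correlation of 0.5 and 85 per arm, the SE of the adjusted difference is 5 × √0.75 × √(2/85) = 0.66. The shift is therefore 0.08 to 0.25 of an SE, in favour of the intervention.

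**The case against.** The strongest reply is that these are two levels of exit rather than two opposed rules. Section {11b} itself separates leaving the intervention from leaving the study, so it foresees that some patients will leave. Section {11a} only says what might become necessary. Current suicidality is an exclusion criterion at entry, so possible withdrawal when it emerges later is coherent safety logic. This stands: a reader might infer a flat contradiction, and the wording does not support that. What remains is that no criterion tells a site which exit applies.

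A reader might also infer that primary outcomes are lost beyond recovery. That goes too far. Missing primary values are imputed, and the nurse documents each session, so start status up to exclusion should usually be known.

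A third inference would be that such patients leave the full analysis set, because its definition refers to the exclusion criteria and suicidality is one of them. On the ordinary reading, those criteria describe eligibility at entry, and a crisis after randomization removes no one.

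Nor is bias towards the intervention shown. Controls are treated in the same hospitals and practices and can also be admitted and lost. Starters may still contact the nurse until week 16, so the concentration in non-starters is an inference.

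A guideline for the counseling process is mentioned and may say more about escalation; it is not shown, so this carries only partial weight. Finally, acute inpatients may be unreachable under any rule, which limits what a change can recover. That is correct.

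**Conclusion.** The point holds as an unresolved inconsistency. The plan permits exclusion from the study after a crisis seen by the nurse, handles overlapping deterioration elsewhere by continuing follow-up, and gives no rule for choosing. The route to exclusion is open in one arm only and acts mostly before first use, so arm-specific loss of outcomes is possible. Net imbalance is not established.

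The real exposure lies in the complete-case analyses of week-16 DiGA use and PHQ-9. At 1% to 2% exclusion the effect is small even in the worst case: a nominal 5% one-sided error of at most about 6.0%, a null OR of at most 1.03, and a PHQ-9 shift of at most a quarter of an SE. For the primary endpoint, the error figure applies only if the SAP imputes at the arm's observed rate; counting these patients as non-starters removes it. The exclusion rate, PHQ-9 elevation, SD and correlation are all assumptions, and nothing in the documents supports a rate as high as 5%.

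**What to change.** In {11a}, replace the reference to study exclusion with discontinuation of the intervention under {11b}, and leave the care decision with the clinicians. Require that DiGA start status be recorded at that time. State that week-8 and week-16 outcomes continue to be collected in both arms unless consent is withdrawn or the treating clinician judges contact inappropriate. In the latter case, record the reason and the last known start status.

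The cost is a short wording amendment. Recruitment began in July 2024, so it has to go to the ethics committees and sites by the route in {25}. No visits are added, since {18a} already plans follow-up by telephone interview or online survey, and the sample size is unchanged. Some PHQ-9 values will still be missing for patients in acute crisis; the main gain is a recorded start status and fewer avoidable losses. Priority is low to moderate.
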